#### Secondary outcomes

*i. Episodes of sepsis in the first 2 weeks: *

a) Culture positive systemic infection will be defined as microbiologically positive cultures of blood, cerebrospinal fluid or suprapubic aspirate of urine plus clinical signs of sepsis.

b) Culture negative infection will be defined as clinical signs suggestive of sepsis and considered to warrant >48 hours of antibiotics but with negative cultures.

***ii. Growth: ***All babies will have measurements of weight, length and head circumference at birth and every seven completed days after recruitment until EDD. Growth will be assessed as change in weight, length and head circumference standard deviation score (SDS) from birth to 28 days using conditional charts.

***iii. Incidence of necrotizing enterocolitis: ***defined as radiological evidence of necrotizing entercolitis assessed by consultant radiologist.

***iv. Retinopathy of prematurity: ***All these babies will be routinely screened, for retinopathy of prematurity and will be graded using the internationally recognised grading system [44,45]. Infants will be classified by the most severe degree of retinopathy.

***v. Incidence of intracranial haemorrhage: ***defined as cranial ultrasound evidence as assessed by Consultant Neonatologist.

***vi. Chronic lung disease: ***defined as respiratory support or oxygen dependency at 36 weeks corrected gestational age [46].

*vii. Death within and including the first 28 days after delivery*

***viii. Days of neonatal intensive care***: As defined by BAPM 2002[47].

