### Statistics

Intention to treat analyses will be performed comparing the outcome of all infants allocated to early insulin treatment compared to those allocated placebo, regardless of how complete treatment was. Statistical analyses will use standard methods to calculate the event rates, time-to-event rates, relative risks, and numbers needed to treat for each outcome in the treatment compared with placebo group, along with 95% confidence intervals. Where appropriate χ2, Fisher's exact or log rank tests of significance will be performed and presented with p-values.

The primary outcome will be modelled with logistic regression in order to evaluate a 95% confidence interval for odds ratio according to treatment group adjusted for key prognostic variables, including if significant, geographic centre. No formal interim analyses are intended although the trial's Data Monitoring Committee (DMC) will meet regularly, have access to unblinded data and would recommend early termination to the Trial Steering Committee ifjudged appropriate based on ethical, safety or efficacy considerations. Time to event analyses stratified by category of birthweight, using Kaplan-Meier survival analyses and stratified logrank tests will be used to assist DMC decision-making. For the secondary outcomes, modelling with either multiple regression (for continuous variables) or logistic regression (for binary variables) will be employed, adjusting for the same baseline covariates as the primary analysis. If individual terms in models are non-significant at level 0.05, then simpler models may be presented instead.

A secondary analysis will be on an "as treated" basis, defining treatment exposure as at least 4 days without interruptions of more than 1 hour.

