### Power calculation

Sample size is based on the primary outcome variable of mortality. This is based on statistical power analyses for mortality of 20% by EDD. To predict an absolute difference of 10% with 80% power at the 5% level of significance we would need 428 patients. Non-compliance is not likely to be a problem, although withdrawal from treatment may be 5–10%. Thus we aim to recruit 500 patients. Each unit has an admission rate of approximately 100 very low birth weight babies per year. Due to the confined period of recruitment being within 24 hours of delivery we predict 50% availability for recruitment (some babies will be transferred in after delivery). Coupled with an estimated 60% rate of consent we predict we would recruit 500 infants over a 2 year period with a realistic safety margin. For the primary outcome measure of mortality by EDD loss to follow up should be negligible.

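### Lung disease at 36 weeks, retinopathy and 28-day growth exist only for infants alive to be assessed, yet the all-allocated comparison takes no account of death, so a survival difference could distort them

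*Protocol article*

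**What the plan says.** In the protocol article, Secondary outcomes, item vi has chronic lung disease "defined as respiratory support or oxygen dependency at 36 weeks corrected gestational age". Item iv, on routine screening for retinopathy, states: "Infants will be classified by the most severe degree of retinopathy". Item ii states: "Growth will be assessed as change in weight, length and head circumference standard deviation score (SDS) from birth to 28 days". None of the three includes death or places an infant who dies before the assessment. Death is counted separately, by the expected date of delivery (EDD) as the primary outcome and by 28 days as item vii.

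The Statistics section commits to intention-to-treat analyses "comparing the outcome of all infants allocated to early insulin treatment" with those in the comparison arm. It promises relative risks and numbers needed to treat for each outcome, and multiple or logistic regression for the secondary outcomes. It names no composite and no rule for deaths.

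The Power calculation section says: "This is based on statistical power analyses for mortality of 20% by EDD". It continues: "To predict an absolute difference of 10% with 80% power at the 5% level of significance we would need 428 patients". After an allowance for withdrawal: "Thus we aim to recruit 500 patients".

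**The concern.** An infant who dies before 36 weeks has no lung disease status at 36 weeks. One who dies before day 28 has no 28-day growth, and one who dies before screening is complete may have no final retinopathy grade. An all-allocated comparison of lung disease or retinopathy can then be met literally only by leaving those infants in the denominator as non-events. Otherwise it becomes a comparison of survivors, who are no longer the groups that were randomised.

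This matters more here than in most trials because the design itself expects mortality to halve. The Background says that lower mortality must not be bought with more long-term morbidity, so these outcomes act as the check on the primary result. The Discussion says that infants of 1–1.5 kg were included for possible benefit on growth and retinopathy, two of the three affected outcomes. It also says that both mortality and morbidity are much lower in that weight band than below 1 kg. Deaths averted may therefore fall mainly among infants with the highest morbidity, although the article gives no figures for this.

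**Working it through.** **The plan's own figure.** For 20% v 10%, two-sided 5%, 80% power and 1:1 allocation (sidedness and ratio are not stated, so both are assumed), the usual two-proportion formula gives 199 per arm, 398 in all. With continuity correction it gives 219 per arm, 438 in all, within 3% of 428. Fisher's exact test at 214 per arm has 80.1% power. So 428 reproduces, and 20% v 10% is the effect the trial is built on.

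**Who can be assessed.** At 250 per arm, deaths by EDD are 250 × 0.20 = 50 on control and 250 × 0.10 = 25 on insulin, leaving 200 and 225 survivors. Deaths by EDD stand in for deaths before 36 weeks, which the article does not give.

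**Model.** Suppose that 80% of infants survive under either arm, 10% survive only with insulin (the saved infants) and 10% die under either. Let b be the risk of chronic lung disease (CLD) in those who survive either way, and k·b the risk in saved infants. Insulin has no effect on CLD itself. The article gives neither b nor k, so both are assumptions.

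- All randomised, deaths as non-events: control 0.8b, insulin 0.8b + 0.1kb. Relative risk (RR) = (0.8 + 0.1k)/0.8.
- Survivors only: control b, insulin (0.8b + 0.1kb)/0.9. RR = (0.8 + 0.1k)/0.9.
- Death or CLD: control 0.2 + 0.8b, insulin 0.1 + 0.8b + 0.1kb.

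The first two RRs do not depend on b. With b = 40%:

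| k | All randomised | RR | Survivors only | RR | Death or CLD | RR |
|---|---|---|---|---|---|---|
| 0.5 | 32% v 34% | 1.06 | 40% v 37.8% | 0.94 | 52% v 44% | 0.85 |
| 1 | 32% v 36% | 1.125 | 40% v 40% | 1.00 | 52% v 46% | 0.885 |
| 2 | 32% v 40% | 1.25 | 40% v 44.4% | 1.11 | 52% v 50% | 0.96 |

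For b from 20% to 50% and k from 1 to 2, the composite RR runs from 0.78 to 1.00.

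**Chance of a nominally significant result against insulin** (unadjusted two-proportion test, b from 20% to 40%). All randomised: 9–16% at k = 1 and 21–46% at k = 2. Survivors only: 2.5% at k = 1, which is the nominal rate, and 8–15% at k = 2.

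**True benefit that would be hidden.** Setting the observed RR to 1, a true relative reduction in CLD of 1 − 0.8/(0.8 + 0.1k), or 11–20% for k from 1 to 2, would vanish with all randomised as denominator. In survivors only it is 1 − 0.9/(0.8 + 0.1k), or 0–10%.

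**Opposite direction.** If insulin raised mortality by 5 points, from 20% to 25%, and the extra deaths carried ordinary CLD risk, the all-randomised RR would be 0.75/0.80 = 0.94. That is an apparent benefit caused by deaths.

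**Smaller mortality effect.** With both planning rates halved (10% v 5%), the all-randomised RR is (0.90 + 0.05k)/0.90, that is 1.06 at k = 1 and 1.11 at k = 2. In survivors only it is (0.90 + 0.05k)/0.95, that is 1.00 and 1.05.

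**The case against.** The strongest reply is that this is only an omission. A journal article may leave denominators and the handling of deaths to the full protocol or SAP, and the intention-to-treat sentence is about allocation and completeness of treatment, not about scoring the dead. Part of this stands: the article does not say that infants who die count as free of disease, and the finding should not claim so. But the article does fix the outcome definitions, the analysis set, the effect measures and the models. Together these prescribe an all-allocated comparison of outcomes that only the living can have, which is more than a missing detail.

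Death is also reported separately, so a reader would see a survival difference beside the morbidity results. That is true and useful, but it does not correct the relative risks, numbers needed to treat or p-values for morbidity.

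Four stronger readings are tempting and are not supported.

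- A reader might infer that a survival benefit would necessarily appear as more morbidity. Without a treatment effect on CLD, an excess is certain only if deaths are kept as non-events. In survivors it needs saved infants to be sicker than the rest, and a true benefit could offset it.
- A reader might take much larger figures, for instance b = 20% with 90% CLD in saved infants, giving (0.16 + 0.09)/0.16 = 1.56. That is a 4.5-fold risk, and no CLD rate comes from the article.
- A reader might infer that death is treated as censoring for sepsis and necrotising enterocolitis. Kaplan-Meier is named for the data monitoring committee and logrank tests only where appropriate. No such analysis of sepsis or enterocolitis is specified.
- A reader might treat all three outcomes alike. Growth has no value after death, so without imputation it can only be compared in survivors; the direction of bias is not fixed and only deaths before day 28 matter. Retinopathy is affected only by deaths before screening is complete, and no screening age is given.

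Finally, a composite answers a different question from its components, and in the model it falls purely through mortality. This is a reason to add it beside the components, not in their place.

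**Conclusion.** The point holds as a possible distortion of the secondary outcomes, clearest for chronic lung disease. The primary outcome is not affected. Under the design mortality effect and no true effect on lung disease, the spurious relative risk is 1.125 to 1.25 if deaths are kept as non-events and saved infants have one to two times ordinary risk. In survivors only it lies between 0.94 and 1.11 for half to double risk, with no bias at equal risk.

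This rests on 1:1 allocation, deaths by EDD as a proxy for deaths before 36 weeks, no infant dying because of insulin, and assumed risks in saved infants. The Background gives mortality as high as 20% only for infants under 1 kg, and the Discussion calls it much lower at 1–1.5 kg, so the real distortion may be smaller. For retinopathy and growth the mechanism is the same, but the article does not allow its size to be worked out. The plan should be changed, because these outcomes are meant to show that survival is not gained at the cost of morbidity.

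**What to change.** - Add death before 36 weeks or chronic lung disease at 36 weeks, and death before screening is complete or severe retinopathy, as the intention-to-treat comparisons for items vi and iv. Define severe in terms of the grading system already cited.
- Beside each, report the components and the survivor-only rates, with the number assessed as denominator, and mark the survivor-only rates as conditional on survival.
- Label 28-day growth as a survivors' comparison, with a sensitivity analysis that ranks deaths before day 28 below all survivors.

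The cost is analysis wording and a few more tables. Deaths, lung status at 36 weeks and retinopathy grade are already collected. The small downside is that a composite may be dominated by death, so the components must always be shown with it.

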#### Efficacy

***i. Percent of time normoglycaemic: ***All babies will have a continuous glucose sensor *in situ *for the 7 completed days. Sensors will be inserted within 24 hours of birth and left in situ for 7 days from the time of insertion. The sensors will be removed 12 hours after the insulin infusion has stopped. This will take a measure of interstitial glucose every 5 minutes and will give an assessment of glucose control throughout the first week. The percent of time spent with blood glucose <2.6 mmol/l, 2.6–10.0 mmol/l, >10 mmol/l and <4.0, 4.0–8.0 mmol/l, >8.0 mmol/l will be measured.

***ii. IGF-I and IGFBP-1: ***measured in blood taken on Study Days 1, 3, 7 and 28.

**iii) *cytokines: ***measured in blood taken on Study Days 1, 3, 7 and 28.

**iv) *protein catabolism: ***measured by urinary 3-methylhistidine/creatinine ratio on Study day 7.

### Continuation of insulin treatment after 7 days

If a baby becomes hyperglycaemic after the study dose of insulin has been stopped it will be a decision of the doctors responsible for the patients medical care whether insulin should be restarted, what preparation will be used and what dose administered.

### Concomitant therapy

All other therapy considered necessary for the patients welfare may be given at the discretion of the medical staff in charge of the infant's medical care.

### Withdrawal from treatment

A patient will be withdrawn from the study if in the opinion of the Investigator it is medically necessary or if it is the parents wish for a child to be withdrawn. The reason for withdrawal should be clearly documented in the Case Report Form and reported to the co-ordinating centre within 24 hours.

### Follow up

Contact details and hospital identifiers for all patients in all centres will also be collected so that future follow up will be possible. If there are effects on short term growth it will be important to review growth, body composition and insulin resistance in later childhood, as well as neurodevelopmental outcome. As is current practice in early neonatal deaths, in any baby who dies during the study period, the parents would be approached for consent to a post mortem being performed.

### Statistics

Intention to treat analyses will be performed comparing the outcome of all infants allocated to early insulin treatment compared to those allocated placebo, regardless of how complete treatment was. Statistical analyses will use standard methods to calculate the event rates, time-to-event rates, relative risks, and numbers needed to treat for each outcome in the treatment compared with placebo group, along with 95% confidence intervals. Where appropriate χ2, Fisher's exact or log rank tests of significance will be performed and presented with p-values.

The primary outcome will be modelled with logistic regression in order to evaluate a 95% confidence interval for odds ratio according to treatment group adjusted for key prognostic variables, including if significant, geographic centre. No formal interim analyses are intended although the trial's Data Monitoring Committee (DMC) will meet regularly, have access to unblinded data and would recommend early termination to the Trial Steering Committee ifjudged appropriate based on ethical, safety or efficacy considerations. Time to event analyses stratified by category of birthweight, using Kaplan-Meier survival analyses and stratified logrank tests will be used to assist DMC decision-making. For the secondary outcomes, modelling with either multiple regression (for continuous variables) or logistic regression (for binary variables) will be employed, adjusting for the same baseline covariates as the primary analysis. If individual terms in models are non-significant at level 0.05, then simpler models may be presented instead.

A secondary analysis will be on an "as treated" basis, defining treatment exposure as at least 4 days without interruptions of more than 1 hour.

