## Methods/Design

### Study design

The study is a multicentre randomised controlled trial. It is based in 10 neonatal intensive care units and 500 babies will be recruited over 2 years. Very low birth weight babies (VLBW < 1500 g) will be recruited within 24 hours of delivery and followed until expected date of delivery (40 weeks). They will be randomised to either treatment with early fixed dose insulin (0.05 unit/kg/hr) with 20% dextrose to maintain normoglycaemia, or to receive standard neonatal care. Those randomised to treatment will receive a fixed dose of insulin combined with variable 20% dextrose support throughout the first week. Additional insulin will be infused if blood glucose levels are consistently above 10 mmol/l; and an infusion of 20% dextrose will be started if blood glucose falls to <4 mmol/l to prevent hypoglycaemia (blood glucose < 2.6 mmol/l). Controls will receive standard neonatal care. All babies will be monitored using a *MiniMed *continuous glucose monitor for 7 completed days and have a blood sample taken on Study days 1,3, 7 and 28. A urine sample will be collected from all babies on Study day 7 and all babies will have details of their clinical care recorded daily in the first week then weekly until 4 weeks, at 36 weeks corrected age, at expected date of delivery (40 weeks) and at discharge home.

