### Inclusion in the study

If all the inclusion and exclusion criteria are met the patient will be included in the study and allocated a sequential patient number. The randomisation will be stratified by centre, by birth weight (<1000 g, 1000–1500 g), and by gestational age (<25 weeks and ≥25 weeks). A 24 hour internet based randomisation programme will be used which requires user name and is password secure. Treatment with insulin will begin as soon after birth as is possible following randomisation. Patient data will be analysed on the basis of intention to treat. Consent will be taken by a health care professional who has a good working knowledge of the aims and practicalities of the study. Parents will be given a written information leaflet and given the opportunity to read and discuss the information they have been given alone. As patients need to be recruited within 24 hours of delivery, a system of continuing consent will be used over the first 3 days to ensure that parents are happy with the decision to consent to their baby's participation in the study.

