### Measurement of outcomes

#### Primary outcomes

Death on or before expected date of delivery (taken as date considered the most accurate estimate of delivery date).

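### Centre and other stratification factors can leave the primary mortality model because of their p-values; all three should be kept in it regardless

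*Protocol article*

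**What the plan says.** All statements are in the protocol article.

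- **Inclusion in the study:** "The randomisation will be stratified by centre, by birth weight (<1000 g, 1000–1500 g), and by gestational age (<25 weeks and ≥25 weeks").
- **Study design:** "It is based in 10 neonatal intensive care units and 500 babies will be recruited over 2 years".
- **Primary outcomes:** the endpoint is binary, "Death on or before expected date of delivery (taken as date considered the most accurate estimate of delivery date").
- **Statistics, primary outcome:** a logistic regression gives a 95% confidence interval for the treatment odds ratio, "adjusted for key prognostic variables, including if significant, geographic centre".
- **Statistics, secondary outcomes:** these use multiple or logistic regression with the covariates of the primary analysis. The next sentence reads "If individual terms in models are non-significant at level 0.05, then simpler models may be presented instead". It speaks of models in general.
- **Statistics, opening paragraph:** for the outcomes as a group, "Where appropriate χ2, Fisher's exact or log rank tests of significance will be performed and presented with p-values".

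Nothing in the article commits the primary analysis to keeping the three stratification factors.

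**The concern.** Stratified allocation balances the arms on centre, birth weight and gestational age. That balance removes part of the chance variation in the treatment comparison. An analysis that leaves the factors out still counts that variation in its standard error, so the test is conservative and the design's gain in precision is partly unused.

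The article does more than stay silent on this. It fixes a data-dependent rule for one stratification factor (centre) and a permissive one for model terms in general. Two things follow:

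1. Whether centre is adjusted for depends on a test of centre, which is a poor guide to whether it belongs in the model. The design already answers that question.
2. Odds ratios are not collapsible. An odds ratio conditional on the strata and one averaged over them differ even with perfect balance. If terms enter or leave by p-value, the meaning of the reported mortality odds ratio is not settled in advance.

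Because secondary outcomes take their covariates from the primary analysis, the same uncertainty passes to them.

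**Working it through.** **1. The plan's own sample size.** Inputs from Power calculation: 20% against 10% mortality, 80% power, 5% level (taken as two-sided), equal arms (assumed).

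- Normal approximation, per arm: n = [1.960·√(2·0.15·0.85) + 0.842·√(0.16 + 0.09)]² / 0.10² = 199, total 398.
- With continuity correction: n′ = (n/4)·[1 + √(1 + 4/(n·0.10))]² = 219, total 438.
- Exact power of the two-sided Fisher test at 214 per arm: 80.1%.

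The stated 428 is reproduced by Fisher's test. It allows nothing for covariates, so it does not depend on this point.

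**2. Assumptions for the simulation.** From the article: 500 infants, 10 centres, the three stratification factors. Not in the article, so assumed:

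- 50 infants per centre, 1:1 allocation within centre × weight × gestation.
- Shares of 50% (1000–1500 g), 40% (<1000 g and ≥25 weeks) and 10% (<25 weeks).
- Control mortality in those groups, A: 8/25/50%, or B: 12/28/40%.
- Between-centre SD of 0, 0.3 or 0.6 on the logit scale.
- Treatment log odds ratio −0.95 (A) or −0.85 (B).

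Overall control mortality without centre variation is 0.5·8 + 0.4·25 + 0.1·50 = 19.0% for A and 0.5·12 + 0.4·28 + 0.1·40 = 21.2% for B. The corresponding treated mortality is 9.0% and 10.7%. Both are close to the planned 20% against 10%.

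**3. Results** (3,000 null and 1,500 alternative trials per row; Monte Carlo standard error about 0.4 points for type I error and 0.7 for power). Each cell gives type I error / power in %. Unadjusted is the range over χ², Fisher, log-rank and crude logistic.

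| Scenario, centre SD | Unadjusted | Weight + gestation, no centre | Terms kept only if p<0.05 | All strata kept |
|---|---|---|---|---|
| A, 0 | 2.9–3.5 / 89.0–90.5 | 4.5 / 92.1 | 4.6 / 92.1 | 4.8 / 92.7 |
| A, 0.3 | 3.1–3.8 / 89.7–90.9 | 4.6 / 92.5 | 4.9 / 92.7 | 5.2 / 93.0 |
| A, 0.6 | 2.8–3.5 / 90.6–91.8 | 4.5 / 92.9 | 5.3 / 93.5 | 5.3 / 93.7 |
| B, 0.3 | 3.6–4.2 / 91.0–91.8 | 4.9 / 92.5 | 5.1 / 92.6 | 5.2 / 92.8 |

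- *Ignoring all strata* costs between 92.8 − 91.8 = 1.0 and 92.7 − 89.0 = 3.7 points of power. The upper end includes Fisher's own conservatism; crude against fully adjusted logistic regression loses about 1.1 to 2.4 points.
- *Dropping centre alone* costs 0.3 to 0.9 points.
- *Selecting by p-value* costs 0.2 to 0.7 points.
- *Stability of the rule:* centre was kept in 5–6% of trials at SD 0, 28–37% at SD 0.3 and 77–85% at SD 0.6. Gestational age was dropped in 8–16% of trials under A and 62–67% under B.
- *Disagreement:* the seven analyses disagreed about p < 0.05 in 1.9–2.7% of null trials and 2.0–3.9% of trials with an effect. Taking the smallest of the seven p-values gave type I error of 4.9–5.5%.

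**4. Which odds ratio is reported.** Take a conditional odds ratio of 0.45 in every stratum and no centre variation.

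- A: treated mortality by stratum 3.77/13.04/31.03%, overall 10.2%. Marginal OR = (0.102/0.898)/(0.190/0.810) = 0.48.
- B: 5.78/14.89/23.08%, overall 11.2%. Marginal OR = (0.1116/0.8884)/(0.212/0.788) = 0.47.

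With centre SD 0.6, integrating over the centre effects gives about 0.50 (A) and 0.485 (B).

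**The case against.** The strongest reply is that little is at stake. The selected model, which is what the rule produces, keeps its type I error and loses under one point of power in these scenarios. The larger losses come from not adjusting at all, which the article does not propose for the primary model. The sentence on simpler models follows the secondary outcomes and is permissive. Birth weight and gestational age are the obvious key prognostic variables, and strong predictors are usually kept.

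Most of this stands as a limit on size. It does not remove the point: the condition on centre is attached explicitly to the primary model, the later sentence refers to models without restriction, and gestational age was often dropped when its assumed effect was weaker.

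Stronger readings that a reader might infer, and that the document does not support:

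- **The treatment term itself could be removed.** The model's stated purpose is an interval for the treatment odds ratio, so this reading defeats the text.
- **χ², Fisher and log-rank form a menu for the primary endpoint.** That sentence is generic across outcomes; the primary outcome has its own sentence naming logistic regression.
- **The covariates are improperly left unnamed.** An article may leave that list to the full protocol or analysis plan.
- **Type I error is materially inflated.** The simulations do not show it. A wider pool of unnamed covariates was not examined.
- **The loss is larger.** Stratum mortality of 45/13/5% with centre SD 0.4 and an odds ratio of 0.45 gives 63% power unadjusted against 68–69% adjusted. With the 10/40/50 split those rates imply only 4.5 + 5.2 + 2.5 = 12.2% control mortality, well below the planned 20%. At 20% against 10% with 250 per arm, unadjusted power is about 88%.

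**Conclusion.** The point holds in a limited form. Centre, a stratification factor, enters the primary model only if significant, and a general sentence lets other non-significant terms go. This is a stated rule, and an analysis plan that always kept centre would contradict it.

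The consequence is modest and mostly conservative: type I error of 2.8–4.2% and about 1–4 points of power lost when the strata are ignored altogether, against 4.8–5.3% and 92.7–93.7% power when all are kept. The case for change rests mainly on fixing the model and the meaning of its odds ratio in advance, since the power cost of selection itself is small. All figures depend on the assumed stratum shares, stratum mortality and centre variation, none of which the article gives.

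**What to change.** In Statistics, specify one primary analysis: logistic regression of death by expected date of delivery on treatment, birth-weight stratum, gestational-age stratum and centre, all retained whatever their p-values. Fit centre as a random intercept, or pool small centres by a rule set without reference to outcome by arm. Delete the significance condition on centre and the sentence permitting simpler models. Use the same fixed covariates for the secondary outcomes. State that unadjusted χ², Fisher and log-rank tests of mortality are supportive.

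The cost is wording and slightly more analysis work; no new data and no change to the sample size are needed. The practical burden is sparse centres: at 20% against 10% one expects about 500 × 0.15 = 75 deaths, or 7 to 8 per centre, so the handling of centre should be settled before outcomes are compared by arm.
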